#### EORTC QLQ-C15-PAL

The EORTC QLQ-C30 is one of the most frequently used questionnaires to measure health-related quality of life in cancer patients. Its short version (EORTC QLQ-C15-PAL) was specifically designed for the application in palliative care settings [27]. The questionnaire consists of 15 items measuring nine of the original instrument’s subscales *(global health status/quality of life, physical functioning, emotional functioning, fatigue, nausea/vomiting, pain, dyspnoea, insomnia, appetite loss, constipation)* on fourteen 4-point scales *(0 = “not at all”, 1 = “a little”, 2 = “quite a bit”, 3 = “very much”),* in addition to the patient’s global health status/quality of life on a 7-point scale *(1 = very poor, 7 = excellent).* The EORCT QLQ-C15-PAL is administrated once at baseline and a second time after completion of both sessions. We use the German translation provided at the EORTC’s website [28].

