Hence, the general aim of the present study is to improve the body of research on this important but underrepresented topic. More precisely, the study goals are to evaluate the effectiveness of a music therapy relaxation intervention regarding palliative care patients’subjective perception of relaxation, well-being, and pain (i.e. immediate effects on psychological outcomes; primary outcome of this study),autonomous relaxation response indexed by HRV and BVP (i.e. immediate effects on physiological outcomes),health-related quality of life (i.e. medium-term effects).

Therefore, we compare the effects of music therapy to the ones of a control group, using a prerecorded mindfulness exercise without musical elements or therapeutic interaction. We hypothesize improvements over time in both groups, but a superiority of the music therapy intervention on all three aforementioned dimensions.

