### Study design and procedures

The study is designed as a prospective RCT with two parallel arms. Hospitalized patients eligible for study inclusion are contacted at bedside in their rooms and informed about the procedures and objectives of the study. The investigator presents the purpose of the study as to compare the effects and feasibility of two commonly used relaxation interventions for the palliative care context. No information is given about which of the two interventions is the actual experimental condition. If patients agree to participate, the investigator asks them to sign the informed consent sheet, and baseline assessment of the patients’ QOL and previous experience with relaxation techniques is obtained. Following that, the investigator gathers relevant information from the patients’ medical record and opens a serially numbered opaque envelope containing assignment to one of the two study arms (see interventions). We used a computer-based block permutation for the generation of the randomization sequence before the onset of the study. The investigator then returns to the patients’ room with the physiological measuring devices, collects pretest data on relaxation, well-being, and pain using VAS, and starts a 5-minute pretest recording of HRV. Then, either the experimental condition (music therapy) or the control condition (verbal relaxation) is initiated, lasting for twenty minutes. HRV is recorded throughout this procedure. Data collection is complemented by another five minutes of HRV recording and posttest VAS assessment following the intervention. The entire procedure lasts thirty minutes and is repeated two days later, finishing with the follow-up assessment of patients’ QOL. In both groups, the patient rests in a supine position for the entire duration of the session. Figure 1 shows a flow diagram of the study design and procedures.

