#### Verbal relaxation

The verbal relaxation intervention uses a 20-minute excerpt from Jon Kabat-Zinn and Ulrike Grossmann’s CD “Stressbewältigung durch die Praxis der Achtsamkeit”^b^
[25], adopted from the *mindfulness-based stress reduction* (MBSR) program. MBSR is a structured 8–10 weeks group program that has shown to effectively improve the physical and mental health of participants from different medical and non-medical contexts by training participants’ self-awareness and mindfulness [26].

The control condition’s time-frame is identical to the experimental condition (5 min. baseline → 20 min. intervention → 5 min. postline). The standardized application of the intervention utilizes a conventional MP3 player and stereo headphones and therefore, requires no additional personnel. The investigator stays silently inside the room, in case the patient expresses unease or wants to cancel the intervention. The prerecorded MBSR track lasts twenty minutes and contains a body scan and breathing exercise, spoken by a soft, female voice. After completion, the investigator asks the participant to remain in his position for the 5-minute posttest HRV recording and VAS assessment.

Figure 2 provides an overview of the procedures and time course of the experimental and control condition.

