### Data analysis

#### Sample size calculation

Statistical power calculations for this study are adjusted for immediate short-time effects on self-report VAS data (i.e. the primary outcome). Bradt and Dileo’s [8] findings suggest that medium sized effects are most likely to be expected for the impact of music therapy on psychosocial outcomes in palliative care. Recent articles [29, 30] on sample size calculations emphasize the superiority of ANCOVA models for analyzing the results of randomized, controlled trials over the repeated-measures ANOVA approach. The inclusion of pretest values as a covariate in these models increases statistical power (i.e., the likelihood to identify statistically significant effects).

Assuming statistical power of (1-β) = .80, type-I error probability of α = .05, and a correlation between covariate and outcome of ρ = .6, a total sample size of *N* = 84 is required to detect medium sized effects between groups [29]. With an expected drop-out rate of 10%, approximately 92 participants need to be recruited for this study. The risk of attrition bias will be addressed in the course of intention-to-treat analyses.

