#### Statistical analyses

We will test for significant differences between groups at baseline using independent samples t-tests, with α = .20 to reduce type-II error probability. For all study hypotheses tests, type-I error probability is set to α = .05. VAS and QOL data will be analyzed with ANCOVA models, where posttest values serve as criteria, pretest scores as covariates and group assignment as a fixed predictor, respectively. We will run repeated-measures ANOVA on physiological data (HRV/BVP) to test for polynomial trends over time, main effects of group allocation, and interaction effects.

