## Discussion

This paper presents the study protocol of a randomized controlled trial on the psychological and physiological effects of a music therapy relaxation intervention for terminally ill patients in palliative care.

One crucial aspect of clinical trials in palliative care research is the design of an adequate control group condition. Different authors took controversial stands regarding the ethical justifiability of applying rigorous, quantitative research methodology in general, and random assignment to study arms in particular to populations of terminally ill patients [31–33]. Withholding potentially effective treatments due to randomization can be particularly problematic. Therefore, we decided to include an active control treatment instead of a no treatment or treatment as usual condition. The experimental and control group intervention share one possible factor of therapeutic change, namely the concept of mindfulness, which is present in both interventions. Hence, if significant between-group differences are to appear, they need to be attributed to factors unique to the music therapy treatment. These are associated with social aspects or the therapeutic relationship on the one hand and characteristics of the live-played music itself, both inherent parts of the definition of music therapy as a health-care profession [5]. Hence, we believe this study design to be appropriate to evaluate the effectiveness of the music therapy relaxation intervention described above. In the course of the analysis and discussion of the study results, we will have to address the question of how the comparison of two active treatments affects the interpretation of our findings. We discuss methodological challenges associated with the implementation of clinical controlled trials on the effectiveness of music therapy in palliative care in more detail in a recently published article [34].

As the study is not supported by external sponsors, no resources for additional study personnel are available. Hence, we expect a long data collection period. As with all interventional studies in palliative care, high drop-out rates are likely to become a particular issue that must be handled in the course of sensitivity analysis.

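### The only follow-up QOL form is scheduled after both sessions are completed, so patients who miss or stop session 2 have no planned QOL endpoint

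*Protocol article*

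**What the plan says.** Two sections of the protocol article set the time of the follow-up QOL assessment, and they agree. Under Outcomes (EORTC QLQ-C15-PAL), the questionnaire "is administrated once at baseline and a second time after completion of both sessions". Under Study design and procedures, the session "is repeated two days later, finishing with the follow-up assessment of patients’ QOL". No other QOL assessment after baseline is described, and none is described for a patient whose second session does not take place or is broken off.

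Four other statements bear on this:

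- Statistical analyses: VAS and QOL are analysed by ANCOVA, "where posttest values serve as criteria, pretest scores as covariates and group assignment as a fixed predictor".
- Sample size calculation: "The risk of attrition bias will be addressed in the course of intention-to-treat analyses". Expected drop-out is put at 10%.
- Discussion: "high drop-out rates are likely to become a particular issue that must be handled in the course of sensitivity analysis".
- Verbal relaxation: the investigator stays in the room "in case the patient expresses unease or wants to cancel the intervention", so a session that is not finished is foreseen.

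QOL is the third of the three dimensions on which the Background section hypothesises superiority. It is labelled a medium-term effect and is not the primary outcome.

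**The concern.** Whether follow-up QOL is observed depends on something that happens after randomisation, namely reaching and finishing session 2. In a palliative care unit, patients who do not get that far are likely to differ from those who do. If they have no form, the QOL comparison is between those well enough and willing to finish in each arm, not between the groups as randomised.

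The reasons for losing session 2 need not be the same in the two arms. Music therapy needs a therapist at the bedside, while the verbal relaxation needs a player and headphones. The Discussion says that there is no money for extra study staff.

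How missing values are imputed, and which sensitivity analyses are run, can properly be left to an analysis plan. When the form is handed out is a different matter. It is a data-collection rule that the article states twice, and no later analysis plan can recover forms that were never collected.

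**Working it through.** **1. The stated schedule, followed for one patient.** A patient is randomised, has baseline QOL and session 1, and then declines or is too unwell for session 2.

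- Study design and procedures: the form comes at the end of the repeated session. That point is not reached.
- EORTC QLQ-C15-PAL: the form comes once both sessions are completed. That condition is not met.
- Statistical analyses: the posttest is the dependent variable. Without it the patient contributes nothing to the ANCOVA unless a value is imputed.
- Any imputation would be built from completers only, because no patient without session 2 would have an observed follow-up QOL. Its key assumption could not be checked.

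**2. The plan's own figure.** Inputs from Sample size calculation: power 0.80, α = 0.05, ρ = 0.6. Assumed because not stated: medium effect = 0.5 SD, two-sided test, equal allocation.

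- Residual SD = √(1 − 0.6²) = 0.8.
- n per arm = 2 × [0.8 × (1.960 + 0.842) / 0.5]² = 40.2, so 41 per arm, 82 in total. One more per arm gives the stated 84.
- Recruitment: 84 × 1.1 = 92.4 and 84 / 0.9 = 93.3, both close to the stated figure of about 92.

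The figure reproduces. It was derived for the VAS, and this point does not alter it.

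**3. Bias of a completers comparison.** In each arm let p be the share without follow-up QOL, and d how much worse their QOL is than completers', in SD, after baseline adjustment. The full-arm mean is the completers' mean minus p × d. With M for music therapy and C for control:

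bias = p_M × d_M − p_C × d_C

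The documents give neither p by arm nor d. Their only related figure is the 10% overall drop-out. Illustrations, all on assumed inputs:

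| p_M / p_C (either way round) | d in both arms | Absolute bias |
|---|---|---|
| 10% / 10% | any equal value | 0 |
| 5% / 15% | 0.5 | 0.10 × 0.5 = 0.05 SD |
| 5% / 15% | 1.0 | 0.10 × 1.0 = 0.10 SD |

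The sign depends on which arm loses more of its sicker patients.

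**4. Precision.** Illustration only, since QOL was not the basis for sizing. With 92 randomised and the assumptions in step 2 (noncentral t), power for QOL is:

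| Share without QOL | Analysed | Power |
|---|---|---|
| 0% | 92 | 0.84 |
| 10% | 82.8 | 0.80 |
| 20% | 73.6 | 0.75 |
| 30% | 64.4 | 0.69 |

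At the stated 10% the loss is small. It matters only if drop-out is as high as the Discussion fears.

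**The case against.** The strongest reply is that both passages describe the normal flow for a patient who follows the schedule. Neither says that the form is withheld from others. The article is condensed, and procedures for patients who stop early may stand in the full protocol. This has force: the wording may give a time and not a condition. But the time given is the only one, and an investigator working from it reaches the form only at the end of session 2. A clarifying sentence is needed on either reading.

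Three stronger readings are tempting, and the documents do not support them.

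- A reader might infer that the promised intention-to-treat analysis turns into a completers analysis. The article does not say so. It announces intention-to-treat and sensitivity analyses, and the intention-to-treat sentence stands in the section that sizes the trial on the VAS. The VAS is rated before and after each session, so session 1 data survive the loss of session 2.
- A reader might infer that an intention-to-treat QOL analysis is impossible. It is possible with imputation, though on assumptions that cannot be tested.
- A reader might infer a bias worth a sizeable part of the target effect. Any such figure rests on assumed inputs. Adjustment for baseline QOL removes the part of the deficit that baseline predicts. The 0.5 SD yardstick belongs to the VAS. A session lost because the therapist was unavailable may say little about the patient's health. The documents give no reason why loss through illness should differ by arm.

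**Conclusion.** The point holds in a limited form. The schedule as stated leaves patients who miss or stop session 2 without an observed QOL endpoint. The QOL ANCOVA would then rest on completers, or on imputation without any observed data from non-completers, in a trial that commits itself to intention-to-treat and expects substantial drop-out.

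It touches QOL only. The primary outcome and N = 84 stand.

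The size of any bias cannot be derived from the documents. It may be zero, and the 0.05 to 0.10 SD shown above depends wholly on the assumed 5%/15% split and the assumed deficit. Nor would a better rule recover everyone: patients who are too ill or no longer reachable stay missing whatever the schedule says. This is a cheap improvement to a non-primary outcome, not a flaw that threatens the trial's main result.

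**What to change.** Amend Study design and procedures and the EORTC QLQ-C15-PAL section so that the follow-up form is sought on the day session 2 is due (two days after session 1). It should be sought from every randomised patient who is reachable and has not withdrawn consent to data collection, whether or not session 2 was given or finished. Record the reason when the form is not obtained. Analyse QOL as allocated in all patients with the form.

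The cost is one sentence in the procedures and a little extra collection work: a 15-item form on a day when the investigator is already due to see the patient. The observed QOL effect may come out slightly smaller, because some patients will have had only one session. Treatment and sample size do not change.

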### Data analysis

#### Sample size calculation

Statistical power calculations for this study are adjusted for immediate short-time effects on self-report VAS data (i.e. the primary outcome). Bradt and Dileo’s [8] findings suggest that medium sized effects are most likely to be expected for the impact of music therapy on psychosocial outcomes in palliative care. Recent articles [29, 30] on sample size calculations emphasize the superiority of ANCOVA models for analyzing the results of randomized, controlled trials over the repeated-measures ANOVA approach. The inclusion of pretest values as a covariate in these models increases statistical power (i.e., the likelihood to identify statistically significant effects).

Assuming statistical power of (1-β) = .80, type-I error probability of α = .05, and a correlation between covariate and outcome of ρ = .6, a total sample size of *N* = 84 is required to detect medium sized effects between groups [29]. With an expected drop-out rate of 10%, approximately 92 participants need to be recruited for this study. The risk of attrition bias will be addressed in the course of intention-to-treat analyses.

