**Methods/design:**

A sample of 84 participants from a palliative care unit in Heidelberg is randomized to either two sessions of music therapy or two sessions of a verbal relaxation exercise, each lasting 30 minutes. The music therapy sessions consist of live played monochord music and a vocal improvisation, the control group uses a prerecorded excerpt from the mindfulness-based stress reduction program containing no musical elements. Outcome measures include self-report data on subjective relaxation, well-being, pain intensity, and quality of life, as well as continuous recording of heart rate variability and blood volume pulse as indicators of autonomous nervous system functioning.

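### The abstract randomises 84 patients, but the sample size section needs 84 after drop-out and recruits about 92 (exactly 94)

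*Protocol article*

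**What the plan says.** The Sample size calculation section of the protocol article sets out its inputs as follows: "Assuming statistical power of (1-β) = .80", "type-I error probability of α = .05" and "a correlation between covariate and outcome of ρ = .6". It concludes that a total of 84 "is required to detect medium sized effects between groups". The allowance for losses comes next: "With an expected drop-out rate of 10%, approximately 92 participants need to be recruited for this study". In that section, 84 is therefore the number needed after drop-out and about 92 the number to enter.

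The Methods/design paragraph of the abstract reads: "A sample of 84 participants from a palliative care unit in Heidelberg is randomized to either two sessions". It does not mention 92 or drop-out.

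Study design and procedures puts the opening of the allocation envelope after consent, the baseline questionnaire and a look at the medical record, and before the first session. The article describes no run-in or later screening step between recruitment and randomisation.

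**The concern.** The same number, 84, has two roles. In the abstract it is the number randomised, before any loss. In the sample size section it is the number required, with an allowance for loss added on top. Because allocation comes so soon after consent, most losses would fall after randomisation, so a gap between recruitment and randomisation does not explain the difference.

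If the abstract's figure were the one acted on, the trial would have no drop-out allowance and would miss its own power target at its own assumed loss rate. The step from 84 to 92 also looks like multiplication by 1.1 rather than division by 0.9, which falls slightly short of replacing a 10% loss.

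**Working it through.** **Inputs stated in Sample size calculation and Statistical analyses:** power 0.80; α = 0.05; pretest–posttest correlation ρ = 0.6; required N = 84; drop-out 10%; about 92 to recruit. On the model: "VAS and QOL data will be analyzed with ANCOVA models", with the pretest score as covariate.

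**Inputs not stated, assumed here:** d = 0.5 for a medium effect, a two-sided test, and 1:1 allocation. A one-sided test gives N = 64 by the normal approximation, so two-sided is the reading that fits the plan's figure.

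**Step 1. Reproduce the plan's 84.**
- An unadjusted two-sample t-test at d = 0.5 needs 64 per arm.
- The ANCOVA variance factor is 1 − ρ² = 1 − 0.36 = 0.64.
- 64 × 0.64 = 40.96, rounded up to 41; adding 1 per arm gives 42, so N = 84.
- Check by noncentral t, with df = N − 3 and noncentrality (d/√(1 − ρ²)) × √(N/4) = 0.625 × √(N/4): power is 0.798 at N = 82 and 0.808 at N = 84.

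The stated N reproduces, with less than one percentage point to spare above 80%.

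**Step 2. Drop-out allowance.**
- Number needed so that 84 remain after 10% loss: 84/(1 − 0.10) = 93.3, or 94 in two equal arms (47 each). Then 94 × 0.9 = 84.6 remain.
- The stated figure matches 84 × 1.1 = 92.4. Then 92 × 0.9 = 82.8 remain, which is 84 − 82.8 = 1.2 short.

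**Step 3. Power under each entry number, at the plan's own 10% loss.**

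| Randomised | Expected evaluable | Power |
|---|---|---|
| 94 | 84.6 | at least 80.8% (the value at 84) |
| 92 | 82.8 | 80.2% |
| 84 | 84 × 0.9 = 75.6 | 76.5% |

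Only the last row misses the target, by 80 − 76.5 = 3.5 percentage points.

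**The case against.** The sample size section is where the recruitment target is set, and it says about 92. The abstract is a summary, and its 84 equals the required N, so the likeliest explanation is that the authors carried that figure over. Nothing in the methods text says recruitment stops at 84. On that reading the 76.5% never arises. The gap between 92 and 94 is two patients, the text says approximately, and power at 82.8 evaluable still exceeds 80%.

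Most of this stands. It makes the inflation slip minor and the low power figure conditional. It does not remove the inconsistency: the abstract's verb is about randomisation, and the article does not say that its 84 means patients analysed.

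Two stronger readings are tempting, and the document does not support them.

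- **That the trial will fall short of its required sample.** Under the stated target of 92 the expected shortfall is about one patient and the power goal is still met. A material shortfall follows only if 84 is the operative number.
- **That the Discussion contradicts the 10% assumption.** It warns that "high drop-out rates are likely to become a particular issue that must be handled in the course of sensitivity analysis". That is a general caution about palliative care trials and carries no figure, so it cannot be set against 10% as a contradiction. The power calculation also concerns immediate VAS effects, rated before and after each session. Loss on that outcome may be lower than loss over the whole study, although the article does not say so. Power at higher loss rates would be a reviewer's preference rather than a correction.

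**Conclusion.** The enrolment number is stated inconsistently and should be reconciled. If 84 is literally the number randomised, the plan's own 10% loss leaves about 76 evaluable and power of about 76.5% against a stated 80%. If about 92 is the target, the plan does what it claims to within about one patient, and the only fault is that the exact allowance is 94.

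The power figures rest on d = 0.5, a two-sided test and 1:1 allocation. These are assumptions, supported by the fact that they reproduce N = 84. The inconsistency between the two sections and the division by 0.9 do not depend on them. Severity: minor.

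**What to change.** Give one number to randomise, in the same words, in the abstract and in the sample size section. Any of these would do:

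- 94 randomised (47 per arm), for 84 evaluable at 10% loss;
- 92 randomised, stating about 83 evaluable and power of about 80%;
- if 84 is the real randomisation target, stating about 76 evaluable and power of about 76.5%.

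The cost is a wording correction and, in the second and third options, a slightly less favourable figure in print. No extra patients are needed if the figures are only restated. Choosing 94 means two more patients than 92, or ten more if 84 was the operative number. Ten is not trivial for a single-unit trial without external funding that already expects slow data collection.
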